## Abstract

Background

Root ZX3, a high-frequency dental generator introduced in 2021, utilizes high-frequency current (HFC) within the root canal to coagulate and incinerate pulp tissue in seconds. Despite its clinical potential, evidence regarding its specific application for symptomatic irreversible pulpitis (SIP) remains scarce. This study aims to evaluate the safety and clinical effectiveness of Root ZX3 for the management of SIP in a dedicated clinical trial. Specifically, the primary objective is to assess the immediate relief of spontaneous pain (primary endpoint) and the incidence of adverse events following HFC application.

Methods

In this single-center, single-arm trial, we will include 10 permanent teeth diagnosed with SIP. Following infiltration anesthesia and dental dam isolation, an access cavity will be prepared to allow the Root ZX3 tip electrode to contact the pulp tissue. After the HFC application, the cavity will be sealed with a temporary restoration. Our primary endpoint is the resolution of spontaneous pain on postoperative day 0, defined as the proportion of participants achieving complete relief.

Discussion

SIP-related emergencies often disrupt clinical workflows due to their unscheduled nature. The treatment time is a critical bottleneck in these scenarios. By employing Root ZX3, clinicians may manage SIP more efficiently without increasing chair time or affecting other patients. If this protocol proves effective and safe, Root ZX3 will offer a valuable technical alternative for the immediate management of acute pulpitis.

Conclusion

This clinical trial will provide the first systematic evaluation of the Root ZX3’s HFC application for managing SIP. By leveraging its ability to rapidly coagulate pulp tissue in anatomically complex areas, this approach aims to streamline the emergency endodontic workflow without compromising patient safety or treatment precision. Although this exploratory study is limited by its single-center design and small cohort, the results are expected to provide a critical foundation for optimizing pain-relief protocols. Ultimately, demonstrating the effectiveness of Root ZX3 could establish it as a valuable, time-efficient option for the immediate relief of acute pulpal pain in busy clinical settings.

## Introduction

Pulpectomy is one of the most common treatments for symptomatic irreversible pulpitis (SIP). According to clinical guidelines published in the Journal of Endodontics, pulpectomy remains the primary treatment for SIP, alleviating symptoms such as spontaneous pain, percussion pain, and others [1]. This approach is supported by the American Association of Endodontists' position statements on treatment planning for endodontic cases [2,3]. In clinical practice, many patients with SIP present without an appointment, requiring their emergency treatment to be performed within an already busy clinical schedule. It can be challenging to completely remove dental pulp tissue due to the complex anatomy of the root canal system. Residual pulp tissue after pulpectomy may cause postoperative pain, including occlusal pain, percussion pain, or pain during root canal preparation. Furthermore, performing root canal treatment within limited time frames may increase the risk of complications, such as pulp floor perforation, ledge formation, or file fracture, due to the need to rush the procedure. Deviations in root canal morphology, such as perforations or ledges, may complicate subsequent root canal treatment and could adversely affect the outcomes of retreatment should it become necessary [4,5]. Additionally, although preservation of peri-cervical dentine and minimally invasive root canal treatment are increasingly emphasized, root canal treatment undertaken under time pressure may also lead to excessive removal of cervical dentine [6].

In 2021, J. Morita Manufacturing (Kyoto, Japan) launched the Root ZX3, a next-generation apex locator [7]. While it serves primarily as a high-precision device for root canal measurement, it features an optional high-frequency module capable of generating high-frequency current (HFC; 530 kHz). By attaching this module, the device can utilize HFC within the root canal to coagulate and incinerate dental pulp tissue within a few seconds. The device can coagulate and incinerate pulp tissue even in complex, narrow root canals that cannot be entirely removed by mechanical instrumentation; however, clinical evidence regarding the use of Root ZX3 for the management of SIP is lacking. To assess the safety and efficacy of the Root ZX3 in managing SIP, this single-center, single-arm clinical study was developed.

## Materials and methods

Trial design

This is a single-center, open-label, single-arm clinical trial. The PICO (Population, Intervention, Comparison, and Outcome) framework for this study is summarized in Table 1. To ensure comprehensive reporting, this protocol adheres to the Standard Protocol Items: Recommendations for Interventional Trials (SPIRIT) criteria [8]. We have included the finalized SPIRIT checklist in the Appendix.

**Table 1 TAB1:** PICO question SIP: symptomatic irreversible pulpitis; HFC: high-frequency current

Criteria	Description
P (Participants)	Patients with a tooth diagnosed with SIP
I (Intervention)	Application of HFC
C (Control)	Not applicable (single-arm trial)
O (Outcome)	Proportion of spontaneous pain resolved after intervention

Participant timeline

The schedule of enrollment, interventions, and assessments is summarized in Table 2.

**Table 2 TAB2:** SPIRIT figure

Timepoint	Enrolment &	Assessment 1	Assessment 2
	intervention	(Day 1, 2, 3, or 7	(Two weeks after intervention
	(Day 0)	after intervention)	range ±7 days)
Enrolment			
Eligibility screening	X	―	―
Informed consent	X	―	―
Intervention			
Intervention	X	―	―
Clinical assessment			
Inspection	X	―	X
Pain during treatment	―	―	X
Percussion	X	―	X
Adverse events	X	―	X
Questionnaire survey	―	X	―

Study setting

All clinical trial activities will take place at Nagasaki University Hospital in Nagasaki, Japan.

Sample size

As the clinical application of Root ZX3 for SIP lacks systematic evaluation, no preliminary data are available for a formal power calculation. This study is therefore designed as an exploratory, single-arm feasibility trial to obtain initial estimates of safety, effect size, and clinical variability.

A total sample size of 10 participants was selected based on feasibility requirements for early-phase device investigations, in which small cohorts (typically 10-20) were appropriate for identifying procedural concerns before larger trials. Given the absence of prior effect-size estimates for immediate postoperative pain relief with this device, a formal calculation would lack a meaningful basis. Data from these 10 cases will provide the necessary preliminary estimates to determine the power and sample size for future multicenter randomized controlled trials.

Eligibility screening

Eligibility will be confirmed by operators in accordance with the criteria listed in Table 3.

**Table 3 TAB3:** Eligibility criteria SIP: symptomatic irreversible pulpitis; VAS: visual analog scale

Inclusion criteria	Exclusion criteria
Participants with a tooth	Participants with pacemakers or implantable cardioverter-defibrillators
diagnosed with SIP requiring pulpectomy	
Permanent teeth	
Teeth with spontaneous pain	
Teeth with a positive response to an electric pulp test	
Participants aged ≥18 years	
Participants who can complete the VAS assessment independently	
Teeth without periapical lesions	
Periodontal pocket depth of the target tooth <4 mm	
Absence of furcation lesions in the target tooth	
Alveolar bone resorption of the target tooth	
< one-third of the root length	
Participants who provide written informed consent	

Intervention

After enrollment, the following procedure will be performed by operators. Following infiltration anesthesia, the targeted tooth will be isolated with a dental dam, and an access cavity will be prepared in the SIP tooth's pulp chamber using a rotary cutting instrument. Only minimal pulp exposure will be created to allow insertion of the electrode tip. The tip electrode of Root ZX3 was then inserted into the pulp tissue, and HFC (Mode 4; 530 kHz) was applied three times. The access cavity will be sealed with a temporary restorative material (Caviton; GC Dental Industrial Corporation, Tokyo, Japan). Finally, a questionnaire assessing post-treatment pain will be provided to the patient.

If the target tooth presents with extensive caries and severe structural loss, it will be temporarily built up with composite resin to facilitate isolation and treatment; thereafter, the above intervention will be carried out. Any other usage of high-frequency electrosurgery instruments during treatment with Root ZX3 will be prohibited.

At 2 ± 1 weeks after the intervention, the pain questionnaires will be collected, and horizontal and vertical percussion was evaluated by operators. Then, pulpectomy was performed without infiltration anesthesia to assess pain during treatment. After the study, procedures are completed, participants were followed up as part of routine care, and appropriate treatment was provided as needed.

All intervention procedures will be documented in the electronic medical record by the operators to enhance protocol adherence. Criteria for halting the intervention include a participant’s request to withdraw or modify their assigned treatment, any clinical deterioration or onset of comorbid conditions, and any situation where the research team deems continued participation unsuitable.

Primary endpoint

The primary endpoint is the relief of spontaneous pain on postoperative day 0. The primary outcome will be expressed as the proportion of participants in whom spontaneous pain has completely resolved on postoperative day 0.

Secondary endpoints

The secondary endpoints are: (1) Relief of spontaneous pain on postoperative days 1, 2, 3, and 7; (2) Improvement in occlusal pain on postoperative days 0, 1, 2, 3, and 7; (3) Pain during pulpectomy was experienced two weeks after the intervention; (4) Improvement in percussion pain two weeks after intervention.

Safety endpoints

For devices in this category, the following adverse events require particular attention: burns, convulsions, muscle contractions, tissue and mucosal injury and inflammation, hematoma, electric shock, cardiac arrest, and perforation. To date, such adverse events have not been reported with Root ZX3. All adverse events will be recorded and assessed for severity and causality.

Data collection

After the intervention, participants will be given a pain diary to record their pain levels and the dose and frequency of any analgesic medication taken. Spontaneous, occlusal, and percussion pain will be evaluated using a questionnaire. Postoperative Pain Assessment on postoperative day 0 was conducted after the effects of local anesthesia had completely worn off, typically 4 to 6 hours following the procedure. Occlusal and percussion pain will be assessed via a 100 mm visual analog scale (VAS; endpoints defined as 100 for unbearable pain and 0 for no pain), and participants will be instructed to indicate their pain level by marking the VAS line. Operators will assess pain during pulpectomy, which will be performed two weeks after the intervention. For percussion testing, clinical operators will conduct both vertical and horizontal percussion using the blunt end of a dental mirror handle to evaluate the status of the periodontal ligament and periapical tissues. To ensure force consistency and provide a baseline for the participant, the test is first applied to an adjacent or contralateral healthy tooth with a gentle, controlled tapping force. The participant’s response is then recorded using a VAS. These assessments are conducted at baseline (Day 0) and at the two-week follow-up visit.

Data management

Upon obtaining written informed consent, the operator will complete the identification and case registration forms. These documents are subsequently integrated into the electronic medical record and forwarded to the Principal Investigator (PI), who maintains them within the secure research file. To ensure participant confidentiality, a unique research identification number, consisting of a numeric code and a symbol, is assigned to each participant upon enrollment. This identifier is deliberately kept separate from any personal information, such as initials or medical record IDs, that could directly identify an individual.

All study-related documentation, including case report forms, will be managed exclusively using these identification numbers to maintain anonymity. While the PI utilizes these codes for general data handling, a master identification list, linking names and medical record IDs to their respective study codes, will be maintained separately. This list is stored in a secure, lockable cabinet for a minimum of five years post-study, ensuring that participant identification remains possible only when strictly necessary and authorized.

Statistical design

The proportion of participants in whom spontaneous pain is resolved on postoperative days 0, 1, 2, 3, and 7 will be calculated using all enrolled cases as the denominator and the number of participants whose spontaneous pain has resolved as the numerator. The mean, standard deviation, median, minimum, maximum, and quartiles of preoperative and postoperative occlusal pain (VAS values) were calculated on days 0, 1, 2, 3, and 7, and those of percussion-induced pain (VAS values) will be calculated at 2 ± 1 weeks postoperatively. Fisher's exact test will analyze the presence or absence of occlusal pain (based on VAS values) on postoperative days 0, 1, 2, 3, and 7, as well as the presence or absence of improvement in percussion-induced pain (based on VAS values) at 2 ± 1 weeks postoperatively, compared with baseline. The proportion of participants with pain at 2 ± 1 weeks postoperatively will be calculated by using all cases as the denominator and the number of participants with pain as the numerator.

Participants who discontinue participation in the study will be excluded from the efficacy analysis. Data with missing values are not discarded and are subject to statistical analysis.

Access to data

The final dataset generated by this study will be accessible exclusively to the PI. Direct access for other research personnel is not permitted under this protocol.

Monitoring

A designated research staff member will conduct monitoring based on standard operating procedures, delivering findings to the PI within 14 days of the evaluation. Should any adverse events or unforeseen complications arise, the PI will provide medical intervention, notify the CRB, and brief the study team. Given that Root ZX3 has already received approval from the Pharmaceuticals and Medical Devices Agency, a separate data monitoring committee is not required.

Potential benefits and harms

Reducing treatment time may lessen the burden on both participants and operators. If this study demonstrates that Root ZX3 alone is effective in managing SIP, it may expand treatment options and potentially benefit a wide range of patients. Possible side effects of the intervention include: (i) burns; (ii) spasms and muscle contractions; (iii) tissue and mucous membrane damage and inflammation; (iv) tissue injury; (v) burns or injury to other parts of the body of the participants due to improper contact with the counter-rod; (vi) hematoma; (vii) hypersensitivity to electric stimulation; (viii) cardiac arrest; (ix) iatrogenic injury to surrounding tissues; and (x) perforation.

Potential device malfunctions include: (i) ignition or explosion of flammable substances or gases; (ii) unintended output; (iii) unintended power increase or configuration change; (iv) malfunction due to electromagnetic interference; (v) malfunction due to wire breakage; (vi) malfunction due to poor contact; (vii) high-frequency shunt or leakage; (viii) interference with other equipment due to electromagnetic wave; and (ix) malfunction of an implantable cardiac pacemaker or implantable defibrillator. All such risks will be explained to participants during the consent process.

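### Adverse events that arise and settle between Day 0 and the two-week visit have no scheduled prospective capture, although adverse-event incidence is part of the primary objective

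*Protocol article*

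**What the plan says.** - **Objective.** The Abstract (Background) says that "the primary objective is to assess the immediate relief of spontaneous pain (primary endpoint) and the incidence of adverse events following HFC application".
- **Commitment.** The Safety endpoints section says "All adverse events will be recorded and assessed for severity and causality". It names as events needing particular attention "burns, convulsions, muscle contractions, tissue and mucosal injury and inflammation, hematoma, electric shock, cardiac arrest, and perforation".
- **Schedule.** Table 2 has three columns: Day 0, Assessment 1 (Day 1, 2, 3 or 7) and Assessment 2 (two weeks, ±7 days). The adverse-event row reads "Adverse events X ― X". The questionnaire is the only item marked under Assessment 1.
- **Take-home form.** Under Data collection, "participants will be given a pain diary to record their pain levels and the dose and frequency of any analgesic medication taken".
- **Return of the form.** The Intervention section says "At 2 ± 1 weeks after the intervention, the pain questionnaires will be collected".
- **Between visits.** The Monitoring section describes the response if an adverse event arises: medical intervention by the principal investigator, notice to the review board, and a briefing of the team. It sets no contact or safety question between the two visits.

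**The concern.** The trial follows pain on Days 0, 1, 2, 3 and 7, but has no scheduled check for harms between Day 0 and the second visit. An event that starts after the participant goes home and has healed by the visit can reach the data only if the participant volunteers it or remembers it when asked. Missed events can only lower the recorded incidence. That matters because incidence is part of the primary objective, and because the Sample size section says the ten cases are to provide initial estimates of safety and inform later randomized trials.

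**Working it through.** The plan has no computed figure to reproduce here: the sample size of 10 is a feasibility choice and no event rate is assumed. The check is mainly a comparison of sections.

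**1. When adverse events are looked for.** Table 2 gives two occasions. The second is at 14 ± 7 days: 14 − 7 = Day 7 at the earliest and 14 + 7 = Day 21 at the latest.

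**2. How long recall has to last.** For an event on day *d* and a visit on day *v*, recall spans *v − d* days. An event on Day 5 with a visit on Day 7 needs 7 − 5 = 2 days. An event on the evening of Day 0 with a visit on Day 21 needs about 21 days. So 7 to 21 days is the time from intervention to visit, and about three weeks is the longest recall, not the typical one.

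**3. Which listed events fall in the gap.**
- Convulsions, muscle contractions, electric shock, cardiac arrest and perforation would be expected during access or current application. Day 0 has both an adverse-event check and an inspection.
- Tissue or mucosal injury, inflammation and hematoma can appear or become noticeable later. So can a burn: the current is applied under infiltration anesthesia, and Data collection says its effect typically lasts 4 to 6 hours. The article does not say at what point on Day 0 adverse events are checked.
- Of this second group, whatever is still present at two weeks can be found by the inspection marked there. What has resolved cannot.

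**4. Whether the form fills the gap.** As described, the diary covers pain levels and analgesic use. Painful inflammation would leave some trace there. A painless hematoma or a small mucosal lesion would not.

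**5. Scale, under assumed values.** The documents give neither a true event rate *p* nor a share *s* of events captured, so both are assumptions. The chance of recording at least one event in 10 participants is 1 − (1 − *ps*)^10.

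| Assumed *p* | *s* = 100% | *s* = 75% | *s* = 50% |
|---|---|---|---|
| 10% | 1 − 0.900^10 = 65.1% | 1 − 0.925^10 = 54.1% | 1 − 0.950^10 = 40.1% |
| 20% | 1 − 0.800^10 = 89.3% | 1 − 0.850^10 = 80.3% | 1 − 0.900^10 = 65.1% |

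If 0/10 is recorded, the one-sided 95% upper limit on the true rate is (1 − 0.05^(1/10))/*s*. This gives 25.9% with full capture, 25.9/0.75 = 34.5% at 75% capture, and 25.9/0.50 = 51.8% at 50% capture.

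These figures show the direction of the effect and its sensitivity to capture. They do not estimate what will happen in this trial.

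**The case against.** The strongest reply is that two scheduled checks plus unscheduled reporting are defensible for a single-session procedure with an approved device. Inspection and percussion also have a dash under Assessment 1, which fits a column with no clinic visit and does not show that reported events would be ignored. The promise to record all adverse events is not limited to visits, the Monitoring section has a standing response, and the Potential benefits and harms section says the risks are explained at consent. The Conclusions already say that the safety profile must be validated in larger trials.

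Most of this stands, and it rules out several stronger readings that a reader might infer:
- *That the most relevant days are uncovered.* Several of the listed events, including the gravest, belong to Day 0, which is covered.
- *That safety data rest on one to three weeks of recall.* That range is the visit window. Recall for a given event can be much shorter, and spontaneous reports are not excluded.
- *That the diary asks about nothing but pain and analgesics.* The article says what the diary records. It does not say nothing else is asked, and the form is not shown.
- *That events needing action would be learned of only weeks later.* The documents do not support this; such events are the likeliest to prompt contact.
- *That the gap is shown by the contrast between 1/10 (exact 95% interval 0.3–44.5%) and 0/10 (0–30.8%).* Any single missed event in any ten-person study gives that contrast.

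What the reply does not remove is the explicit dash in the adverse-event row. That is a stated schedule rather than a detail left to a fuller document, and a standing response acts only on events that someone reports.

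**Conclusion.** The point holds in a limited form. Delayed, self-resolving adverse events have no scheduled prospective capture between Day 0 and a visit on Day 7 to 21. They depend on spontaneous report or on recall of at most about three weeks, so the incidence named in the primary objective may be under-counted, and any error runs towards fewer events. The size is unknown. The conclusion assumes that Table 2 reflects the full protocol and that the take-home form contains no safety question beyond what is described; if it does contain one, Table 2 should show it. The pain-relief primary endpoint is unaffected. This is a worthwhile low-cost improvement in how harms are collected, not a flaw that invalidates the trial.

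**What to change.** In Table 2, mark adverse events under Assessment 1. On the take-home questionnaire, add one dated item for each of Days 0, 1, 2, 3 and 7: any new problem since the last entry, yes or no, and if yes a short description. The Day 0 entry should go with the pain assessment made after the anesthesia has worn off, so that it picks up injuries not felt in the clinic. No new visit is needed, since participants already fill in the form. The cost is one extra line on the form, an edit to Table 2, and the work of recording and grading a few more minor events.

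### The day-0 success rule counts pain-free participants regardless of analgesic use, so the planned proportion is only an upper bound on relief without analgesics

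*Protocol article*

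**What the plan says.** All references are to the protocol article.

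- **Primary endpoint:** "The primary outcome will be expressed as the proportion of participants in whom spontaneous pain has completely resolved on postoperative day 0". No condition on analgesic use is attached.
- **Statistical design:** the proportions for days 0, 1, 2, 3 and 7 "will be calculated using all enrolled cases as the denominator", with "the number of participants whose spontaneous pain has resolved as the numerator". Again there is no analgesic condition.
- **Data collection:** participants keep a diary to "record their pain levels and the dose and frequency of any analgesic medication taken". This is the only mention of analgesics in the document. The day-0 rating is made "after the effects of local anesthesia had completely worn off, typically 4 to 6 hours following the procedure".
- **Intervention:** the one stated restriction on concomitant care is "Any other usage of high-frequency electrosurgery instruments during treatment with Root ZX3 will be prohibited".
- **Potential benefits and harms:** one sentence begins "If this study demonstrates that Root ZX3 alone is effective in managing SIP". Under Anticipated results, the hypothesis is that HFC application produces a high rate of complete relief on day 0.
- **Trial design and Sample size:** single arm, open label, 10 participants, no formal power calculation. The results are to supply estimates for sizing later randomised trials.

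**The concern.** The day-0 rating is delayed so that residual local anesthesia does not mask pain. The same delay gives a participant with returning pain several hours in which to take an analgesic. Someone who does so and is pain-free at the rating is a success under the printed rule and is credited to HFC. The later days, which use the same numerator, leave more time for analgesic use.

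The trial collects the data that would show this but gives them no role in any stated endpoint or analysis. In a controlled trial the other arm would at least show how much relief occurs alongside analgesics; here nothing does. At stake are the reading of the primary result as an effect of the device and the estimate passed on to the design of later trials.

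**Working it through.** The document states no expected response rate, success threshold or analgesic-use rate, so there is no planned figure to reproduce. The check is a reading of the rule followed by arithmetic. N = 10 comes from Sample size; every other number below is an assumption for illustration.

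**1. What the rule counts.** Among the 10 enrolled, let A be the number resolved with no analgesic and B the number resolved after taking one. Split B into B1, pain-free only because of the analgesic, and B2, who would have been pain-free anyway.

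- Planned proportion = (A + B)/10
- Analgesic-free proportion = A/10
- Proportion who would be pain-free without analgesics = (A + B2)/10

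Since 0 ≤ B2 ≤ B, the third quantity lies between the other two. The planned figure is too high by B1/10 and the analgesic-free figure too low by B2/10. Each B1 participant therefore adds 1/10 = 10 percentage points to the planned figure.

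The bounds assume that an analgesic never makes a participant worse, and that nobody in A is rated under a dose the diary missed, such as one taken before the procedure.

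**2. Size on the reported scale (assumed counts).** Suppose 8 of 10 report resolution. The proportion, with its exact (Clopper-Pearson) 95% interval, after removing B1 participants is:

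- B1 = 0: 8/10 = 80% (44.4% to 97.5%)
- B1 = 1: 7/10 = 70% (34.8% to 93.3%)
- B1 = 2: 6/10 = 60% (26.2% to 87.8%)
- B1 = 3: 5/10 = 50% (18.7% to 81.3%)

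If B = 3, the planned figure is 80% and the analgesic-free figure 50%. The data alone do not say where between them the value without analgesics lies.

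**3. Expected inflation (assumed rates).** Let p be the share pain-free without an analgesic, u the share of the rest who take one, and r the share of those takers who become pain-free. Counted rate = p + (1 − p) × u × r. With u from 0.25 to 0.75 and r from 0.3 to 0.6, u × r runs from 0.075 to 0.45.

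- p = 0.5: 0.5 + 0.5 × 0.075 = 0.5375 to 0.5 + 0.5 × 0.45 = 0.725
- p = 0.7: 0.7 + 0.3 × 0.075 = 0.7225 to 0.7 + 0.3 × 0.45 = 0.835
- p = 0.8: 0.8 + 0.2 × 0.075 = 0.815 to 0.8 + 0.2 × 0.45 = 0.89

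Across these inputs the inflation runs from 1.5 to 22.5 percentage points.

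**4. Chance that it occurs at all (assumed rates).** If each participant has probability q of being pain-free only because of an analgesic, the chance of at least one among 10 is 1 − (1 − q)^10: 40% at q = 0.05, 65% at 0.10, 89% at 0.20 and 97% at 0.30.

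**The case against.** The strongest reply is that counting resolution regardless of analgesics is a recognised treatment-policy choice, and that an analysis plan not shown may add a supportive analysis. The first part stands: the rule is not an error in itself, which is why the planned proportion should be kept. But the article does not declare that choice, and a treatment-policy proportion does not isolate what HFC did. As to the second part, the article itself states the endpoint, numerator and denominator, so the point concerns a printed rule and not an omitted detail.

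The trial is also exploratory, has no success threshold, and defers definitive efficacy to later randomised trials (Conclusions). That limits the consequence. It does not remove it, because the estimates are meant to feed the sizing of those trials.

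Three stronger readings are tempting, and the document supports none of them.

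- A reader might infer that the diary cannot show whether a dose came before the day-0 rating, because only dose and frequency are named. The form is not shown, so this is not established.
- A reader might take the analgesic-free proportion as the corrected HFC rate. Taking an analgesic is not the same as being relieved by it: some users dose as a precaution or for occlusal pain. The figure is a lower bound. Nor does it separate HFC from opening the tooth or from spontaneous improvement.
- A reader might take the phrase about Root ZX3 alone as a promise of relief without analgesics. In its context, after a sentence on treatment time, it can equally mean the device without immediate pulpectomy. The point does not depend on it.

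**Conclusion.** The point holds in limited form. As printed, the day-0 rule and its counterparts for days 1, 2, 3 and 7 count analgesic-assisted relief as resolution. The planned proportion is therefore an upper bound on relief without analgesics, overstated by 10 percentage points for each participant who is pain-free only because of an analgesic. How many such participants there will be cannot be known from the document, so every figure beyond that 10-point step is illustrative. The conclusion assumes a denominator of all 10 enrolled and no further rule in a document not shown. It should be settled before analysis; it does not call the design or the sample size into question.

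**What to change.** - Keep the planned proportion as defined.
- Pre-specify beside it, for days 0, 1, 2, 3 and 7, the proportion of all enrolled whose spontaneous pain has resolved with no analgesic taken before the rating (day 0) or on that day (later days). Report the number of analgesic users at each time.
- Describe the two figures as upper and lower bounds on relief without analgesics, and base any effectiveness statement, and any estimate passed to later trials, on both.
- Check the diary form. If it does not already capture the time of each dose and of the day-0 rating, add both for the remaining participants. Where timing is unknown, treat any day-0 analgesic use as not analgesic-free.

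**Cost.** One additional proportion and one count per day, with N unchanged. The second figure will be equal or lower and is conservative, because some users would have been pain-free anyway. Recruitment began in August 2025, so a diary change would come mid-trial, and timing may be incomplete for those already enrolled. With recruitment planned to December 2027 and no interim analysis, the rule can still be fixed before the data are analysed. No rule on the use of analgesics is altered.

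### Pain during the two-week pulpectomy is assigned to the unblinded operators with no patient rating or scale, although the participant-marked VAS is already in use at that visit

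*Protocol article*

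**What the plan says.** Secondary endpoint 3 is pain during the pulpectomy at the two-week visit. The Intervention section explains the setting: "pulpectomy was performed without infiltration anesthesia to assess pain during treatment".

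The Data collection section treats the pain outcomes differently:

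- **Occlusal and percussion pain:** "Occlusal and percussion pain will be assessed via a 100 mm visual analog scale", and "participants will be instructed to indicate their pain level by marking the VAS line".
- **Pulpectomy pain:** "Operators will assess pain during pulpectomy, which will be performed two weeks after the intervention". No scale, anchors, question to the participant or definition of pain follows.

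The Trial design section states: "This is a single-center, open-label, single-arm clinical trial". The Intervention section introduces the treatment with "After enrollment, the following procedure will be performed by operators", so the role that treats is also the role that assesses this outcome. Table 3 lists as an inclusion criterion: "Participants who can complete the VAS assessment independently".

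The Statistical design section plans VAS summaries for occlusal and percussion pain only. For the two-week visit it adds: "The proportion of participants with pain at 2 ± 1 weeks postoperatively will be calculated".

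**The concern.** Pain is the participant's own experience. If an operator who knows that the device was used decides whether pain was present, the outcome can reflect the observer's reading as well as the participant's sensation. With no control arm, such a tendency cannot cancel out between groups.

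This endpoint carries weight in the trial's argument. The Introduction names pain during canal preparation as a possible consequence of residual pulp tissue, and the Anticipated results section expects less pain of that origin. The visit is also set up so that this outcome can be observed.

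A bare yes/no result does not separate slight from severe pain. It also gives no spread on a graded scale, although the Sample size section says that the 10 cases should supply initial estimates of effect size and clinical variability for later trials.

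**Working it through.** The plan states no figure for this endpoint, so there is nothing to reproduce. The check is mainly a comparison of sections, followed by a short calculation.

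**1. Who rates, and on what scale.**

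| Outcome | Rating described | Scale | Planned analysis |
|---|---|---|---|
| Occlusal pain, days 0 to 7 | participant marks | 100 mm VAS | VAS descriptives and Fisher's exact test |
| Percussion pain, two-week visit | operator taps, participant's response recorded | VAS | VAS descriptives and Fisher's exact test |
| Pulpectomy pain, two-week visit | operators assess | none named | none by name |

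Percussion and pulpectomy pain belong to the same visit, so the VAS is already in use there.

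**2. Which analysis belongs to endpoint 3.** The sentence on the proportion with pain at 2 ± 1 weeks does not name pulpectomy. The candidates are:

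- Spontaneous pain is analysed on days 0, 1, 2, 3 and 7 only, so it does not fit.
- Occlusal pain is analysed on the same days, so it does not fit.
- Percussion pain at 2 ± 1 weeks already has its own VAS summary and test.
- Pulpectomy pain is what remains.

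This is an inference by elimination. If it is wrong, the article states no analysis for endpoint 3 at all. On either reading no graded summary is planned for it.

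**3. Effect of one reclassified case.** With all 10 cases in the denominator, one case moves the proportion by 1/10 = 10 percentage points. Exact (Clopper-Pearson) 95% intervals for neighbouring results with n = 10:

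| With pain | Proportion | 95% interval |
|---|---|---|
| 2/10 | 20% | 2.5% to 55.6% |
| 3/10 | 30% | 6.7% to 65.2% |
| 4/10 | 40% | 12.2% to 73.8% |
| 5/10 | 50% | 18.7% to 81.3% |

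The counts are illustrative; the article gives no expected proportion. A 10-point shift is small beside these intervals. However, the intervals describe sampling error only: a consistent tendency in how pain is judged would move the estimate without widening them.

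**The case against.** The strongest reply is that operator assessment in this article does not mean operator judgement. The Intervention section also says that operators evaluate percussion, yet Data collection shows that the participant's response goes on a VAS. Table 2 lists percussion and pain during treatment in the same clinical-assessment block, so the table does not settle the matter either. The endpoint itself is worded as pain that was experienced, which fits patient report. The article also condenses a fuller protocol and refers to case report forms that are not shown.

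Much of this stands. A reader might infer that the patient's rating has been replaced by the operator's, or that the same individual treats and rates. The text supports neither: it gives a shared role and leaves the method of asking open. A reader might also infer that the result will be biased in the device's favour by a known amount. No rate of missed pain is given or can be derived, and the participants are unblinded too.

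Nor should a VAS be recommended here for greater precision. A mean in millimetres and a proportion measure different things, so their interval widths cannot be compared directly. A yes/no endpoint is a legitimate choice in itself.

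The reply does not remove the contrast within the article. It states the rater and scale for two pain outcomes, and for the third it names operators and no scale. The Statistical design section then limits VAS summaries to the first two.

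**Conclusion.** The point holds as a worthwhile, inexpensive improvement to a secondary endpoint. As written, the plan allows unblinded operators to judge a subjective outcome and plans no graded data for it, while a participant-marked scale is in use at the same visit and every participant must be able to complete it.

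The only size that can be stated is 10 percentage points for each reclassified case out of 10. The direction and amount of any bias are not established. The yes/no reading rests on elimination. The primary endpoint, spontaneous pain on day 0, is unaffected, and no hypothesis test is stated for endpoint 3.

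**What to change.** 1. In Data collection, state that the participant marks, unaided, one 100 mm VAS for the worst pain during the pulpectomy, recorded at that visit, with the same anchors as the other VAS outcomes.
2. In Statistical design, name endpoint 3 and summarise this score with the statistics already planned for the other VAS outcomes: mean, standard deviation, median, minimum, maximum and quartiles.
3. If the proportion with pain is kept, define its cut-off on that single score before the data are examined. A cut-off of any mark above zero would count a 1 mm mark as pain, so the choice should be deliberate.
4. Keep the operator's note as supporting information.
5. Recruitment began in August 2025 and is planned to run to December 2027. Report separately any participants assessed before the change.

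The cost is one extra VAS mark per participant at a planned visit and a minor form change. A patient VAS takes the observer's judgement out of the endpoint; it does not remove the participant's own expectation effect. The change concerns measurement only, not the clinical conduct of the visit.
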